**Fig. 1 Fig1:**
[figure not shown]
Study flow for participants in the 3for1-project

At the time of the initial manuscript submission, the recruitment phase for this study was ongoing, but not yet completed. Prior to recruiting the first participant, this study, its objectives and hypotheses were pre-registered with the German Clinical Trials Register: DRKS00029002 (registered on 11 May 2022).

### Sample size

We aim to recruit 500 participants, 250 participants per group. Sample size calculation is based on the primary outcome measure at t1 (i.e., employment status 12 months after study entry). Based on a previous longitudinal observational study with unemployed individuals with mental health issues [61], we assume a re-employment rate of 15% with TAU. We aim to achieve a re-employment rate of 30% in the IG. We conducted an a-priori power calculation for this expected intervention effect [62]: Applying a two-sided significance level of α = 0.05 and a statistical power of 0.90, we estimated that *n* = 161 participants in each group are required to show this effect. Based on previous research projects in this subject area, we anticipate a dropout rate of 35% between t0 and t1. To test the intervention effect for the primary outcome, we accordingly require an initial sample size of at least *n* = 248 participants per group at t0.

### Intervention

Participants of both groups will receive TAU within the German social security system; there are no restrictions in terms of concomitant care. This could mean, for instance, that individuals participate in training programs provided by the job center (e.g., application training) or draw on health services such as psychotherapy or medication.

In addition to TAU, the IG will be offered to participate in the 3for1-intervention program and its three components over 12 months after study entry. For intervention utilization, certain time or session limits will be applied in the different components (see below for further details). Participants will be able to choose which of the components they utilize and when: They can choose one, two or three components, concurrently or consecutively. They can make the decision based on their individual needs in order to support self-determination and facilitate intervention motivation and adherence. They will be advised by the local intervention team in their decision. This means that the intervention provider of one component might suggest a suitable other component to utilize concurrently or consecutively based on their experience with the individual participant. The final decision will always lie with the participant. Participation in the intervention overall and the individual components will be voluntary and can be terminated or paused at all times during the 12-months intervention phase. Terminating or pausing participation in one component will not have negative consequences for the participation in the other components.

#### Intervention components

##### Short-term psychotherapy

Participants can receive up to 10 sessions of short-term psychotherapy with a psychotherapist or psychologist with clinical training. Each session will last up to 50 min, which is equivalent to a regular psychotherapy session provided in the German outpatient health care system. In addition to a comprehensive anamnesis and clarifying the participants’ goals of the short-term psychotherapy, the initial sessions will focus on promoting motivation for change. The content of subsequent sessions may vary depending on the formulated goals and can include psychoeducation, developing a bio-psycho-social model of mental illness, resource work, developing a daily or weekly routine, or promoting problem-solving skills, self-efficacy, or social and emotional competencies. Promoting and maintaining motivation to change will be a topic throughout all sessions. Additionally, the indication for further treatment will be assessed. Accordingly, participants may receive a recommendation for further treatment and assistance in finding an outpatient or inpatient therapy place. In the last two sessions, the psychotherapy sessions are reviewed together and the need for booster sessions is assessed. Booster sessions could be indicated for the following goals: relapse prevention, maintenance of treatment gain, refresh learned skills, (re-)assessment of indication for further treatment, or support until continuing treatment starts. Up to three booster sessions can be offered on a case-by-case basis; indication will be discussed in supervision sessions. In general. they will be offered no sooner than two months after the last regular session.

The 3for1-component of short-term psychotherapy will apply an integrative psychotherapeutic approach that combines cognitive-behavioral, systemic, and psychodynamic methods and techniques. According to the competence structure for counseling for depression developed as part of the *Improving Access to Psychological Therapies* program [63], the focus is on therapeutic competencies rather than the selection of specific psychotherapy directions. The short-term psychotherapy component is designed based on the well-established psychotherapeutic consultation in the workplace. These workplace outpatient clinics have been tested as a work-related short-term psychotherapy intervention program and found to be beneficial in terms of symptom reduction [64]. In addition to reducing symptoms specific to certain mental illnesses, the short-term psychotherapy also includes psychotherapeutic methods focused on facilitating re-employment. Findings of previous intervention studies using psychotherapeutic methods in the workplace context indicate the effectiveness and efficiency of such intervention programs in terms of shorter duration until return to work [65, 66]. An important element of the short-term psychotherapy within the 3for1-project is the provision of low-threshold service where individuals can seek counseling without long waiting times and without formal record of utilization with the health insurance.

Each local intervention team will include a 50% full-time equivalent (FTE) psychotherapist or psychologist with clinical training. They will receive intervention-specific training, weekly group supervision, and individual supervision if required. Supervision will be provided by certified psychological psychotherapists and psychiatrists who are members of the research project team.

##### Job coaching

Participants can receive job coaching based on the IPS approach [55, 67]. The IPS approach is a vocational rehabilitation program for individuals with severe mental health issues. The approach implements the principle of *first place*,* then train*, meaning that the job coaching aims to place individuals relatively rapidly in competitive employment in the primary labor market and then trains them at the workplace. In traditional vocational rehabilitation programs, individuals are trained for a considerable amount of time to prepare them for re-entering the workplace. After successful job placement, no further support is usually provided. Based on meta-analyses and reviews, the IPS approach is superior to traditional vocational rehabilitation programs for individuals with severe mental health issues in terms of obtaining and retaining competitive employment [52–54]. IPS job coaching focuses on individual needs and preferences, aiming to find a job and workplace that fits the individual. IPS job coaching involves all aspects of obtaining and retaining employment such as assessment of needs, capabilities, and competencies, individual coaching to obtain employment (e.g., sifting through job offers, creating or revising application documents, accompanying individuals to job interviews), individual coaching to stay in employment (e.g., conducting workplace visits to discuss required adjustments, mediating in conflicts that might arise at the new workplace) as well as building a network of local employers in order to match individuals with suitable employers. IPS job coaching can also include vocational re-orientation. In terms of accompanying individuals to employers, both potential and actual, individuals can always choose for themselves whether they want to disclose their mental health issues to employers; hence they can decide how they would like to explain the job coach’s presence. Discussing the advantages and disadvantages of disclosing mental health issues with individuals is an important part of IPS job coaching as individuals might find employment more easily if not disclosing mental health issues, but then in the long run missing out on reasonable accommodations by an unaware employer [61]. If individuals lose or quit their employment, IPS job coaches discuss the underlying reasons in order to revise their assessment to find a better fitting job in the future. In the 3for1-intervention, participants can receive up to 25 h of job coaching to obtain employment [68]; after obtaining employment, job coaching is unlimited within the 12-months intervention period.

Each local intervention team will include an 80% FTE job coach. All job coaches will work manual-based [55]. They will receive an online training course (https://ipsworks.org/index.php/training-courses/) and a one-day, in-person training course from a German expert in IPS job coaching as well as participate in workplace shadowing in an established IPS unit. Throughout the intervention, they will receive weekly group supervision and individual supervision if needed. Supervision is provided by the same project-internal individuals that provide supervision to the other components. Additionally, job coaches will receive a monthly supervision session by the aforementioned IPS expert external to the team.

##### Peer support

Peer navigators are individuals with lived experience of mental illness and life crises [56]; many have experienced episodes of unemployment, reduced earning capacity or disability pensions. Peer navigators are experts through experience rather than having professional training in health care or social care. An important component of peer support is the disclosure of lived experience with mental health issues in order to create shared lived experience and build a rapport with individuals with mental health issues seeking help [56, 69]. They discuss participants’ needs and aims with them and how they can be fulfilled; in doing so, they focus on individual recovery as a process and empowerment [57]. Peer navigators support participants emotionally and instrumentally in navigating their daily activities, especially within the health care system, social security system, or visits to official authorities. This includes, among others, that peer navigators accompany individuals to appointments with health professionals, in the job center, or debt counseling. Other activities can include activation in daily life (e.g., going for a walk, starting a new hobby) and building a social network (e.g., by joining a self-help group). Peer navigators follow the principle of supporting individuals on equal footing, showing them how they can take control over their lives and help themselves. Peer support is unlimited within the 12-months intervention period.

There will be four peer navigators per local intervention team; each peer navigator will be employed on a marginal part-time employment, which is equivalent to around seven work hours per week. All peer navigators work manual-based (adapted from: [70]) and receive a 1.5-day, in-person training course. Parallel to the other components, they also receive weekly group supervision and individual supervision if required. Supervision is provided by the same individuals as the other components.

##### Integration of components

Each local intervention team consists of a 50% FTE psychologist/psychotherapist, an 80% FTE job coach, and four peer navigators on marginal part-time employment as intervention providers, as well as a 50% FTE researcher who conducts the study onboarding and data collections, and coordinates the local intervention providers. The researcher and intervention providers work as a local team with weekly team meetings where cases are discussed. All team members have equal rights and are encouraged to contribute their own perspective to the cases. Involving other component providers in the cases, where suitable, is encouraged to provide effective individualized support to participants.

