#### Adherence and auditing

Participants can determine which components they use, in what combination and for how long over the 12-months intervention phase. Intervention providers will offer participants regular appointments (i.e., every one to two weeks) with low-threshold scheduling to enable regularity and structure. Although face-to-face appointments are preferred, also in terms if relationship building, intervention providers will offer online appointments as well where necessary. To facilitate face-to-face appointments, reimbursement of travel costs is offered.

Participating in a component can be paused or terminated within the time frame of the 12-months intervention phase. If participants state they would like to pause or terminate participation in one component, intervention providers will stress that the access to that component remains open within the 12-months period and encourage participants to contact intervention providers if their needs change and they would like to resume the component. Additionally, intervention providers will continuously encourage participation in the other two components where considered beneficial. If participants do not use any component for a certain time, research staff will regularly contact them to offer support via the intervention, potentially re-iterating the intervention components.

The intervention providers’ conduct and adherence to intervention manuals will be discussed in regular supervision meetings. Furthermore, every six months, there will be a fidelity assessment for each intervention component to review and, if necessary, further develop high fidelity in each component. The fidelity assessment will be conducted by an internal and an external reviewer based on predefined fidelity scales. Subsequent fidelity reports and emerging barriers will be discussed with the principal investigators and measures taken to improve intervention fidelity further if required.

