#### Primary outcome

The primary outcome is the proportion of participants who are in competitive employment in the primary labor market subject to social insurance contributions 12 months after study entry (yes vs. no). Competitive employment in the primary labor market refers to employment for which anyone can apply and which is not protected or accessible for individuals with disability status only. It will be assessed via self-report as part of the exit interview.

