#### Secondary outcomes

Secondary outcomes encompass variables in relation to (re-)employment, health and well-being, social integration, help-seeking, and self-stigma. These variables will be assessed at t0, t1 and t2 by self-report, predominantly via online questionnaires, but also as part of structured interviews.

We will collect data on various variables related to (re-)employment. We will apply a one-item measure to ask participants about their *motivation to perform paid work* in the primary labor market [20], ranging from 1 (= *low*) to 3 (= *stron*g), with 4 (= *not applicable*,* as currently employed*) specifically for assessment at t1 and t2. Additionally, we will measure how confident participants feel in finding a job, namely job-search self-efficacy (JSSE). Variables regarding current employment status will be measured as self-report at t1 and t2 only (as the inclusion criteria at t0 preclude current employment). More specifically, participants will be asked in the exit and follow-up interview about employment they have started since entering the study or since the exit interview respectively. These questions encompass start and end date of potential employment, type of employment (e.g., part- or full-time employment, self-employment), working hours per week and average monthly net income. Finally, participants will also be asked about measures taken to obtain re-employment since the last assessment.

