### Data collection and management

Assessments will be conducted via structured interviews and online questionnaires at all measurement points. We aim to conduct most interviews in person, but will conduct them via telephone if required and more practical. In particular, the interview six months after study entry on health service utilization will be conducted predominantly via telephone because its short duration would be disproportionate to the travel time to the research sites. Online questionnaires can be completed either on a tablet computer directly in the job center or via a link sent by e-mail. Paper-pencil-versions will be provided as well, in particular for rare technical issues, parallel assessments per research location, or participants with low technological proficiency. Research staff will assist questionnaire completion if needed.

We will employ multiple processes to ensure high quality and completeness of the collected data. Firstly, we selected established instruments for the questionnaires, many have been successfully used in a previous study in a similar population [61]. Regarding employed interview questions, they were discussed and assembled in an iterative process within our research team whose principal investigators have in-depth research experience in the topic area. Secondly, research staff will be trained to administer the questionnaires and conduct the interviews. They will be present when participants complete questionnaires and support them where needed. After measurement points, research staff will check the participants’ responses for completeness, data input mistakes, and apparent inconsistencies. If necessary, they will resolve these together with participants. Thirdly, research staff will meet regularly together with the project coordination and principal investigators to discuss the data collection and to clarify any open questions regarding special cases. This process will ensure high consistency in data collection across the different research sites. Finally, data quality checks will be performed on a regular basis by the biometrical experts within the research team to verify the completeness and plausibility of the data input in the database. Any anomalies in the database will be discussed and resolved within the research team.

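### The local researcher collects outcomes and also coordinates the intervention team, so only intervention-group participants report to someone involved in their programme

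*Protocol article*

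**What the plan says.** The relevant arrangements stand in several sections of the protocol article.

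- **Integration of components.** Each local team includes a half-time "researcher who conducts the study onboarding and data collections, and coordinates the local intervention providers". The section continues: "The researcher and intervention providers work as a local team with weekly team meetings where cases are discussed". It adds: "All team members have equal rights and are encouraged to contribute their own perspective to the cases".
- **Adherence and auditing.** For participants who use no component for a while, "research staff will regularly contact them to offer support via the intervention, potentially re-iterating the intervention components".
- **Primary outcome.** Employment status at 12 months: "It will be assessed via self-report as part of the exit interview".
- **Secondary outcomes.** "These variables will be assessed at t0, t1 and t2 by self-report, predominantly via online questionnaires, but also as part of structured interviews". For each job the interview also records start and end dates, type, weekly hours and net income. Intervention-group participants rate their satisfaction with the programme, and its helpfulness, within the 12-month online questionnaire.
- **Data collection and management.** Of research staff during questionnaires: "They will be present when participants complete questionnaires and support them where needed". Staff then look for gaps, entry errors and inconsistencies and, if necessary, resolve them with the participant. Questionnaires may be done on a tablet at the job center, through an e-mailed link, or on paper.
- **Design and setting.** The control group is passive, receives usual care only, and is recruited before the intervention group.

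The limitations in the Discussion cover non-randomization, developments over time, selective dropout and language. They do not mention the researcher's two roles.

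**The concern.** A participant in the intervention group is asked about symptoms, job-search confidence, employment and satisfaction by a member of the team that discusses their case. A control participant may be asked by the same person, but that person has no part in any programme for them. Polite or hopeful answering, and a generous reading of unclear answers when inconsistencies are settled, can therefore arise in one group only, and would favour the programme.

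The Statistical methods section relies on covariate adjustment to deal with group differences. That can address differences present at baseline. It cannot address a reporting difference that develops during the 12 programme months, because no programme relation exists at study entry.

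At stake are mainly the satisfaction and helpfulness ratings, for which there is no control comparison at all, and the self-rated scales at 12 months (Hypotheses 5 and 6). The trial is meant to inform adoption of the programme as a regular job center service, and these results will be read for that purpose.

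**Working it through.** **1. Does the asymmetry follow from the text?**

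| Feature | Intervention group | Control group |
|---|---|---|
| Outcome data collected by local researcher | yes | probably yes |
| Staff present, check and resolve answers | yes | yes |
| That researcher coordinates the participant's providers | yes | no providers |
| That researcher joins discussion of the participant's case | yes | no case discussion |
| Research staff re-offer the programme to non-users | yes | not applicable |

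The first two rows are common to both groups. The last three differ, so the asymmetry lies in case involvement and not in who holds the questionnaire. One step is inferred: the sections on adherence and on data collection say research staff in general, while Integration of components assigns data collection to the local researcher.

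**2. Which outcomes are exposed?**

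- *Most:* satisfaction and helpfulness ratings, and the 12-month psychosocial scales.
- *Less:* employment status at 12 months. It is a yes/no fact supported by dates, type, hours and income. Some judgement remains over whether a job is competitive and insured.
- *Less:* the 18-month outcomes (Hypothesis 8), taken six months after the programme ends, and the yes/no help-seeking acts within Hypothesis 7.
- *Not exposed:* Hypothesis 4, if taken from the job center records of benefit receipt and duration, and Hypothesis 9, which concerns screening before entry.

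**3. The plan's own figure.** Inputs from Sample size: 15% versus 30%, two-sided 5%, power 90%, dropout 35%. With pooled variance and mean rate 0.225:

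n = [1.96·√(2·0.225·0.775) + 1.2816·√(0.15·0.85 + 0.30·0.70)]² / 0.15² = (1.1575 + 0.7445)² / 0.0225 = 160.8, so 161 per group.

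161 / 0.65 = 247.7, so 248 per group at entry. Both stated figures reproduce and are not in dispute.

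**4. Illustration of sensitivity.** The shifts below are assumptions; the document gives none. Take 161 analysed per group, no true effect, and distortion in the intervention group only. All results are the chance of a significant difference *favouring the intervention*, which is 2.5% without distortion.

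*Employment, true rate 15% in both groups.* Chance = Φ[(δ − 1.96·SE₀)/SE₁], with SE₀ pooled and SE₁ unpooled.

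- δ = 0.03: SE₀ = √(2·0.165·0.835/161) = 0.0414 and SE₁ = √((0.1275 + 0.1476)/161) = 0.0413. Then (0.03 − 0.0811)/0.0413 = −1.24, giving 11%.
- δ = 0.05: SE₀ = √(2·0.175·0.825/161) = 0.0424 and SE₁ = √((0.1275 + 0.1600)/161) = 0.0423. Then (0.05 − 0.0830)/0.0423 = −0.78, giving 22%.
- By the same formula, δ = 0.02 gives 7% and δ = 0.10 gives 61%.

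Three to five points would be 3/15 = 20% to 5/15 = 33% of the planned 15-point difference.

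*A scale score.* SE of a standardized difference = √(2/161) = 0.111. A shift of 0.2 SD gives z = 0.2/0.111 = 1.79, and P(Z > 1.96 − 1.79) is about 43%.

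These figures show how sensitive a trial of this size is to a one-sided reporting shift. They do not estimate the shift that will occur.

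**The case against.** The strongest reply has five parts.

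- **The researcher treats no one.** Therapist, job coach and peer navigators deliver the components, and the participant decides what to use. The re-offer contacts concern people using nothing, who have little reason for courtesy. This stands: a reader might infer that participants report to the person who treats them or runs their programme, and the text supports only coordination and a voice in case discussion.
- **Employment is hard to misreport.** The job details allow an unclear case to be reviewed, staff are trained, special cases go to the principal investigators, and the biometrical experts check plausibility. Receipt of full benefit at 12 months, where the participant consents, is a partial external check. This stands too. A reader might infer that the primary result is materially biased; the document does not show that.
- **Exposure varies.** An e-mailed link lessens contact with staff, and not every outcome under Hypotheses 5 to 8 is equally open to it. This limits the extent, but the interview and the stated staff presence remain.
- **The size is unanchored.** Participants know that they received the programme, so part of any courtesy effect would occur with any interviewer. This stands, and the calculations are therefore illustration only.
- **The obvious remedy could backfire.** Control participants were recruited first. A switch to telephone interviews from another site would fall mainly on the intervention group and make assessor and mode differ by group. Unfamiliar interviewers might also cost retention where 35% dropout is expected. This stands, and a general cross-site rota is not recommended.

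It may also be said that a condensed article leaves interview procedures to the full protocol. That does not answer the point, because the dual role is something the article itself sets out.

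**Conclusion.** The concern holds in limited form. The plan fixes an arrangement in which only intervention-group participants report self-assessed outcomes to a member of their programme's team, and the planned covariate adjustment cannot correct for this. The satisfaction and helpfulness ratings and the 12-month psychosocial scales carry most of the risk. The primary outcome carries less, and the record-based Hypothesis 4 none.

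The direction would favour the programme, but the size cannot be derived from the document. The conclusion rests on two readings: that the local researcher named under Integration of components is among the research staff who attend and check the questionnaires, and that no separate assessor is used, since none is described. It is a weakness of design that can be partly repaired, and neither a contradiction in the plan nor grounds for discounting the primary result.

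**What to change.** 1. **Questionnaires.** Have the 12- and 18-month questionnaires, above all the satisfaction and helpfulness items, completed by link or tablet without the local coordinator present. Staff prompt only for missing items and do not resolve answers. Apply this to all remaining assessments in both groups, and record for each questionnaire the mode and whether staff were present, since control questionnaires already completed cannot be redone.
2. **Primary outcome.** Classify employment from the recorded job fields (start and end dates, type, hours, income) by a fixed written rule, applied by the biometrical team without the group label. Because allocation is by period, supply dates as days since study entry; calendar dates would reveal the group. The rule makes classification even-handed but cannot correct facts that were misreported.
3. **Interviews.** Let an existing researcher from another site do the 12- and 18-month interviews only where both groups can be covered in the same mode. Otherwise keep the local procedure, record assessor and mode, and add the dual role to the limitations in the Discussion.

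The cost is protocol wording, some scheduling effort and possibly slightly more missing items. No additional staff are needed.
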